## Randomisation

After baseline measurements, subjects will be Randomised to three groups at a ratio of 1:1 using a stratified randomisation based on age. Age will be stratified into 3 groups: 4-6, 7-9, and 10-12, in a ratio of 1:2:1.

## Criteria for evaluation

### *Primary efficacy outcome*

- Change in SER with cycloplegic auto-refraction over 12 months

### *Secondary efficacy outcomes*

- Change in AL over 12 months

### *Other outcomes*

- Change in relative peripheral refraction
- Change in choroidal thickness
- Change in accommodative status
- Treatment compliance: lens wear duration per day and number of days per week

Other optometric outcomes not listed here will be considered exploratory in nature.

### *Primary safety outcome*

- Adverse events, including biomicroscopic findings, for the treatment and control groups over 2 years

## Statistical methods

### *Sample Size Calculation*

To achieve a 90% power to detect a 0.315D difference and standard deviation of 0.475D (effect size of 0.658) in SER progression between a treatment group and a control group with an alpha level of 0.05 (2-tailed); the minimum subject number required in each group is 50.

An interim analysis will be performed to evaluate the efficacy on primary and second outcomes at 6 months. To compensate the impact on the final efficacy analysis, Bonferroni adjustment will be performed and the adjusted alpha level will be 0.025. Accordingly, the subject number required in each group is 59 at a 90% power. Assuming a dropout rate of about 10%, at least 65 subjects are required in each group.

### *Statistical analysis*

Data from the right eye will be used for analyses when both eyes show fast progression. If only one eye demonstrated fast progression, that specific eye would be used for analyses. Demographic and optometric data will be displayed as mean and standard deviation, or number and percentage as appropriate. The Chi-square test (or, if appropriate, Fisher's Exact test) and unpaired t-test will be performed to compare baseline between-group differences in demographics (age, sex). Myopia progression will be calculated as the difference between SER and AL at the baseline, the 6-month and the 1-year visits, respectively.

The unpaired t-test will be used to compare the changes in primary and secondary outcomes between groups. The efficacy of myopia control of DIMS lens will be determined by dividing the difference in myopia progression (or axial elongation) between two groups with the myopia progression (or axial elongation) in the SV group, then multiplied by 100%. Multiple regression analysis will be employed to identify factors that may associated with myopia control efficacy.

Data analysis will follow an intention-to-treat approach. Missing values of outcome variables and covariates will be replaced using multiple imputation procedures with 10 sets of imputations assuming missing at random. All analyses will be 2-tailed with a significance level of 2.5%.

The CONSORT Statement will guide the reporting of results.

### **Funding**

The study is jointly funded by The Hong Kong Polytechnic University and Hoya Lens Thailand Ltd. The D1 and D2 spectacle lenses are developed based on DIMS technology in collaboration with Hoya Lens Thailand Ltd.

## 2. Study Plan Schematic

[figure not shown]

Remarks: At each 6-month visit, the criteria for updating the prescription of spectacle lenses for all groups include any of the following:

- Increase in myopia of 0.50D (spherical over-refraction) or more, in either one eye or both eyes
- Habitual visual acuity equal to or worse than 6/9.5, in either one eye or both eyes

An additional spectacle dispensing visit will be scheduled after a prescription update.

### 3. Background and rationale of study

The significant worldwide increase in myopia has ignited increased research interest in predicting and halting myopia development. Myopic defocus has been shown to slow axial growth and myopia progression, primarily based on the principle of simultaneous competing defocus and peripheral optics. Orthokeratology, concentric ring soft contact lenses and DIMS spectacle lens are clinical applications that utilize myopic defocus for slowing down myopia progression in children. However, none of the above was fully effective (~40-60%) in controlling myopia progression.

DIMS technology is developed by PolyU and HOYA. In the 2-year RCT conducted between 2014-2017, DIMS spectacle lens significantly reduced myopia progression by 52% and axial elongation by 62% in schoolchildren aged 8-13 years.

Subsequently, it has been marketed globally under the trade name of MiyoSmart, achieving commercial success due to its non-invasiveness and cost-effectiveness from the customers' perspective. Recently, the joint research team has designed the second generation of DIMS lens (D2) which aims to provide a higher effectiveness compared to the previous design. Despite their higher risk of progressing to higher levels of myopia, limited attention has been given to fast progressing myopes and younger myopes. To explore and enhance the effectiveness of myopia control in these specific groups, both D1 and D2 lenses will be applied as investigational treatments in the current RCT.

### 4. Study Objective

Primary:

- i. To determine the efficacy of D2 lens design in slowing myopia progression in children with fast progressing myopia as compared to SV control.

Secondary:

- ii. To determine the efficacy of D1 lens design in slowing myopia progression in children with fast progressing myopia as compared to SV control.
- iii. To investigate if baseline RPR influences the outcome of myopia control when using DIMS lenses.

- iv. To determine if change of choroidal thickness following short-term DIMS lens wear has a prognostic value in determining the efficacy of myopia control over one year.

## 5. Study Design

### 5.1. Inclusion criteria

The study will enroll participants aged between 4 and 12 years and of Hong Kong Chinese descent. Both eyes of the subjects should have a SER of -0.75D or lower. Except for children aged 4-6 years, documented evidence of fast progressing myopia over the past 2 years, either in terms of SER or AL, is required for enrollment. Documented evidence is defined as past prescription (Rx) forms issued by registered optometrist or registered ophthalmologist within 2 years before the baseline date. Fast progression is defined as a SER progression at a rate of 0.50D/year or more, or an AL elongation at a rate of 0.27mm/year or more in either or both eyes. Documented evidence is selected using the decision tree outlined below.

For children aged 4-6 years without past Rx forms, eligibility requires myopia below the 3rd percentile on refraction curves. Specifically, for 4 to 5-year-olds, their myopia should be -0.75D or below in both eyes. For 6-year-olds, their myopia should be -1.25D or below in at least one eye, with the other eye at -0.75D or below.

BCVA in both eyes should match age norms. For children aged 4-6 years, BCVA of 0.20 logMAR (or its equivalent) or better is necessary, whereas children aged 7-12 years should have BCVA of 0.00 logMAR (or its equivalent) or better. Anisometropia should not exceed 1.50D, and astigmatism should be equal to or less than 2.00D. Participants must demonstrate a willingness to accept random group allocation and adhere to the masked study design. Moreover, they should be able to wear the prescribed spectacles full-time.

[figure not shown]

## 5.2. Exclusion criteria

An individual who meets any of the following criteria will be excluded from participation in this study: individuals with any existing or past eye diseases or surgeries, including but not limited to strabismus surgery, amblyopia, oculomotor nerve palsies, or corneal disease, intraocular disease, or any other conditions that may have an impact on vision or visual development, are excluded; those with binocular vision problems are also excluded. Individuals who regularly intake long-term medication for at least three days per week or use medications or supplements known to affect eye growth are ineligible for the study. Additionally, individuals with systemic diseases that may impact vision or vision development, such as endocrine, cardiac and respiratory diseases, diabetes, Down syndrome, or similar conditions, are excluded. Previous or current treatment for myopia control, such as orthokeratology, progressive addition lenses, myopic defocus lenses, or atropine, is considered as an exclusion criterion. Individuals with allergies to topical anesthetic or cyclopentolate eye drops are not eligible to participate. Finally, individuals who, in the judgement of the Investigator, are unable to cooperate or follow instructions during eye examinations are excluded from the study.

## 5.3. Recruitment

Strategies for subject recruitment include:

1. PolyU optometry clinic and research clinic databases: Identify potential participants through a search of clinic records. Initial contact will be made via telephone. Information regarding study's objectives, procedures, potential risks, and benefits will be verbally introduced to the parent/guardian.
2. Collaborate with schools: Establish partnerships with local schools by offering eye health talks to parents and children. During these talks, information regarding the research study will be introduced. Any concerns or questions from parents can be addressed immediately at the same session. Request permission to include subject recruitment poster in school newsletters or circulars to reach parents.
3. Community outreach: Collaborate with district councils or community service organization to organize eye health talks or vision screenings to raise awareness

about this research study. Any concerns or questions from parents and participants can be addressed immediately at the same session.

4. Online platforms: Prepare advertisements for subject recruitment in the form of a YouTube video and poster. Seek an advertising agency to leverage social media platforms, websites, or online forums popular among parents in Hong Kong to spread the advertisements and reach a larger audience.
5. Parental influence: Invite parents of current or previous subjects from our recent research studies to spread the advertisement for subject recruitment to other parents groups.

#### **5.4. Potential risks**

The eye examination should not result in any undue discomfort. A mild stinging sensation may be experienced for a few seconds when the eye drops for refraction are instilled. The subject may also experience blurry near vision and sensitivity to bright light for about 24 hours after the instillation of eye drops. Therefore, it is suggested to wear sunglasses or a hat while going outdoors. An information sheet regarding the eye drops used in the study will be provided to participants.

The treatment interventions, specifically the spectacle, may induce blurriness, dizziness, and interrupted binocular vision at the first few days of lens wear. A one to two weeks' adaptation period may be required until the symptoms resolved. Upon experiencing persistent discomfort while wearing the spectacle, subjects or parents should report to the Investigators via phone call or message ([name] or [name], [contact]).

#### **5.5. Benefits**

The refractive status and eye health conditions of the participants will be closely monitored by eye care professionals throughout the 2-year study period. The treatment interventions may slow down the myopia progression of the participants. Participants and parents do not need to pay for eye examinations or spectacles.

This research study aims to demonstrate the safety and efficacy of new spectacle lenses in reducing myopia progression in children. A positive outcome is likely to accelerate the global commercialization of this clinical management option, thereby reducing the enormous socioeconomic burden associated with vision loss due to myopia and high myopia.

To express gratitude to the participants and parents for their valuable time and contribution to the research study, they will receive either a pair of single vision spectacles or MiyoSmart spectacles upon completion of the study.

## **5.6. Study intervention**

### **5.6.1. Phase 1: Two-arm RCT**

This study is a double-masked RCT. Subjects and parents are masked from the type of investigational lenses they are wearing. Masked Investigators will be responsible for masked measurements of the primary and secondary efficacy outcomes at the baseline and 6-monthly visits. Masked Investigators will never examine the subjects while they are wearing their spectacle lenses. Unmasked Investigators will conduct the remaining measurements and dispense the investigational lenses.

Eligible subjects will be randomly assigned to the control or the treatment group in an equal ratio. The control group will receive placebo SV lenses, while the treatment group will receive D2 lenses.

Scheduled visits will be conducted over a period of 2 years. The control group will cross over to wear D2 lenses at 12 months and all subjects will continue wearing D2 lenses for an additional 12 months.

### **5.6.2. Phase 2: Auxiliary group**

To compare the efficacy and visual performance of D1 and D2 lenses for internal reference, an auxiliary group having the same number of subjects will be assigned to wear D1 lenses for 2 years. Recruitment criteria, measurement and follow-up intervals of the auxiliary group will be the same as in Phase 1 study.

## **5.7. Randomisation**

Simple randomisation will be implemented by an unmasked Investigator by creating a column of random numbers for the group allocation using Microsoft Excel. Eligible subjects will be assigned to one of the three groups in an equal ratio by following the random sequence generated from Excel. Age will be stratified by 3 groups: 4-6, 7-9 and 10-12, in a ratio of 1:2:1.

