**Exclusion criteria**

- Existing or past eye diseases or surgeries (e.g., strabismus surgery, amblyopia, oculomotor nerve palsies, corneal disease, intraocular disease, etc.) that may have an impact on vision or visual development
- Binocular vision problems
- Long-term medication (intake at least 3 days/week)
- Medication or supplements that affect eye growth
- Systemic diseases that may have an impact on vision or visual development (e.g., endocrine, cardiac and respiratory diseases, diabetes, Down syndrome, etc.)
- Previous or current treatment for myopia control (e.g., orthokeratology, progressive addition lenses, myopic defocus lenses, atropine, etc)

- Allergies to topical anaesthetic or cyclopentolate eye drops
- Individuals who, in the judgment of the Investigator, are unable to cooperate and follow instructions during eye examination.

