### **5.9. Withdrawal criteria**

Subjects (or parents/guardians for subjects <18 years of age) are free to withdraw from participation in the study at any time upon request. No further data will be collected on subjects who withdraw from this study.

If significant intolerance to the treatment intervention is suspected at any time after randomisation, subjects can choose to withdraw or terminate treatment (either treatment or control group).

An Investigator may discontinue or withdraw a subject from the study for the following reasons:

- Significant study intervention noncompliance: unable to contact via 3 phone calls and 3 messages, more than 3 attempts to arrange missed follow-up appointments, wearing the spectacles less than 5 days a week and/or an average of less than 5 hours/day.
- If any clinical adverse event or situation occurs (e.g., allergies to eye drops, reduction of visual function such as diplopia, reduction of BCVA; subject to clinicians' judgement) such that continued participation in the study would not be in the best interest of the subject.

- If the participant meets an exclusion criterion (either newly developed or not previously recognized) that precludes further study participation.

Should subjects require discontinuation of treatment intervention for any reason, follow-up visits and data collection will not continue as scheduled. The reason for discontinuation or withdrawal from the study will be recorded on the Discontinuation/Withdrawal Case Report Form (CRF) in a web-based secure remote electronic database named Research Electronic Data Capture (REDCap). Subjects who signed the informed consent form and were Randomised but did not receive treatment intervention may be replaced. If there are subjects who signed the informed consent form, were Randomised, received the study intervention but were discontinued or withdrawn within the first month due to not meeting inclusion criteria (e.g., unable to tolerate spectacles or eye drops), and it is still within the recruitment period, then these participants' randomisation will be discarded and replaced with a participant from the next allocation. All spectacles (used or unused) will be returned to the unmasked Investigator upon withdrawal or discontinuation from the study.

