### 5.17. Data collection schedules

The following steps will be conducted by study Investigators:

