#### 5.17.1. V1: Eligibility, randomisation and baseline assessment

1. Screen potential participants over the telephone (recorded in electronic spreadsheet)
2. Enter contact details, demographics, and record refractive history (recorded in electronic spreadsheet)
3. Perform baseline assessment on participants for eligibility (recorded in REDCap CRF\_V1)
4. Randomisation of participant (recorded in electronic spreadsheet)

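### Section 5.7 has an unmasked Investigator both generate and run the Excel allocation list, and the protocol states no allocation concealment

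*Protocol*

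**What the plan says.** On the list, Section 5.7 states: "Simple randomisation will be implemented by an unmasked Investigator by creating a column of random numbers for the group allocation using Microsoft Excel". It continues: "Eligible subjects will be assigned to one of the three groups in an equal ratio by following the random sequence generated from Excel".

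On roles at baseline, Section 5.6.1 states: "Masked Investigators will be responsible for masked measurements of the primary and secondary efficacy outcomes at the baseline and 6-monthly visits". Section 5.8 identifies those outcomes as cycloplegic autorefraction and axial length. Section 5.6.1 then says: "Unmasked Investigators will conduct the remaining measurements and dispense the investigational lenses".

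On the sequence of steps, Section 5.17 opens with "The following steps will be conducted by study Investigators". Under that line, Section 5.17.1 lists telephone screening, refractive history, the baseline eligibility assessment (entered in REDCap) and randomisation (entered in a spreadsheet).

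On entry, the exclusion criteria in Section 1 include "Individuals who, in the judgment of the Investigator, are unable to cooperate and follow instructions during eye examination".

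On masking, Section 8.6 describes Investigators, as well as participants, as unaware of allocation.

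**The concern.** Randomisation protects the comparison only if nobody who can affect whether a child enters knows what the child would receive. Someone who can see that the next row is D2 or SV can accept, defer or decline a borderline child in the light of it. The arms may then differ in prognosis before any lens is worn.

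Nothing later in the plan repairs that. Masked measurement of refraction and axial length prevents measurement bias. Intention-to-treat analysis preserves the groups as allocated. Neither restores balance lost at entry. The contrast exposed is the primary one, D2 against SV on 12-month change in SER.

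Section 5.7 is where a reader would look for the safeguard. It names who makes and runs the list, picks an unmasked role for both, and states no safeguard. Concealment is a matter of trial conduct and belongs in the protocol; it is not something normally left to a statistical analysis plan.

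**Working it through.** No figure in the protocol bears on this point. The group sizes in Section 6.1 (50, 59 and 65) neither support it nor change under the fix. The check is a reading of the relevant sections side by side.

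1. **Who makes and runs the list.** Section 5.7 gives both tasks to one role, an unmasked Investigator.

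2. **Whether the list exists before a child arrives.** Section 5.7 has children assigned by following a sequence already generated. Section 5.9 says of certain early withdrawals that "these participants' randomisation will be discarded and replaced with a participant from the next allocation". Both read most naturally as a list prepared in advance.

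3. **What sight of the list is worth.** Under simple randomisation in equal ratio, the next allocation can be guessed with probability 1/3 for three groups (Section 5.7) or 1/2 for two (Section 5.6.1). For anyone who can read the column it is known with probability 1. The protection therefore depends wholly on access to the file.

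4. **Who gathers the eligibility information.** By Section 5.6.1, masked staff supply cycloplegic autorefraction and axial length. The remaining baseline measurements in Section 5.11 fall to unmasked staff. These include BCVA, subjective refraction, binocular vision and ocular health, which is most of what bears on entry.

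5. **How much room for judgement there is.** Many criteria are numeric: SER, BCVA, anisometropia, astigmatism, age and past progression. Some are not: cooperation during examination, binocular vision difficulties with no stated threshold, and ability to wear the spectacles full-time.

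6. **Whether roles are separated.** Section 5.17 gives screening, eligibility assessment and randomisation to the same broadly named group. It neither says that the list-maker screens nor bars it.

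7. **Whether the order of steps helps.** Section 1 (Randomisation) and Section 5.17.1 both put baseline assessment before randomisation. That fixes when an allocation is applied, not when it can be known.

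8. **Whether concealment is stated anywhere.** Sections 5.7, 5.8, 5.17, 6.3 and 8.6 contain no independent list-holder, no central or REDCap release, no sealed envelopes, and no locking of the eligibility decision before the allocation is seen.

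9. **Whether Section 8.6 supplies it.** Taken literally it would mask all Investigators. That cannot be squared with Section 5.6.1, where unmasked Investigators measure and dispense, or with Section 5.7, where one of them makes the list.

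**The case against.** The case on the other side has several parts.

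- **The decision-maker and access to the file are not stated.** This stands. A reader might infer that unmasked Investigators decide eligibility, that the list-maker is among them, and that the spreadsheet lies open to them all. The protocol says none of these. Section 5.6.1 divides measurements, not the entry decision; Section 5.17 speaks only of study Investigators; and nothing describes who can open the file.
- **Discretion is limited.** This largely stands. Most criteria are numeric. Except for some children aged 4-6, fast progression must be documented by registered practitioners' prescription forms, chosen by a decision tree. Masked staff take the cycloplegic autorefraction, which can inform the SER criterion. History, cover test and stereopsis are also scheduled at a screening step before V1 (Section 5.16). This narrows the opening without closing it.
- **Eligibility comes before randomisation, and doing both at one visit is ordinary.** True, and the single visit is not a defect. Order alone is not concealment.
- **Simple randomisation cannot be predicted.** True only for those who cannot see the list.
- **The Manual of Procedures may cover it.** Possibly. Section 5.16 refers to the Manual for each assessment, and randomisation is a row in its table. The Manual is not shown and Section 5.7 does not cite it. If a safeguard exists there, one sentence in Section 5.7 would say so.
- **The project co-ordinator may control allocation information.** Section 8.6 has the co-ordinator authorise unmasking and disclose an individual's allocation in an emergency. That concerns release after randomisation. It does not say who holds the list beforehand.

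**Conclusion.** The point holds in this form: an unmasked Investigator generates and implements the list, no concealment is stated, and roles are not separated. The protocol therefore does not prevent staff who influence entry from knowing the next allocation. Section 8.6 also contradicts Sections 5.6.1 and 5.7 and must be reconciled with them.

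The conclusion rests on reading Section 5.7 as describing a list prepared in advance, and on the protocol's silence about access. It does not claim that any allocation was foreseen or any child's entry steered.

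The size of any bias cannot be estimated. A reader might multiply a guessed share of steered children by the planning SD of 0.475 D and set the result against the planned 0.315 D difference. The protocol gives neither the share steered nor how far such children would differ in expected progression, so such a figure would reflect only its assumptions.

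This should be fixed, as an inexpensive strengthening of the design. It is not evidence that the comparison is already compromised.

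**What to change.** Amend Section 5.7 to state the following:

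- The sequence is generated and held by an existing team member with no part in screening, eligibility or baseline measurement. Alternatively, it is loaded into REDCap with access closed to anyone who takes part in those steps; Section 6.3.1 already describes role-based access there.
- Each allocation is released only after consent and the V1 eligibility CRF are completed and locked.
- A dated screening log records every refusal with its reason.

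Reconcile Section 8.6 with Sections 5.6.1 and 5.7 by naming which Investigators are masked and which are not. For any children already randomised, report how the list was held and who could see it.

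The cost is a procedural amendment, a short wait at V1 while the allocation is released, and some reassignment of roles. The protocol does not say whether the project co-ordinator screens children, so that role's suitability as list-holder needs checking first. No visit, measurement or sample size changes.

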## **Study population**

One hundred and seventy-seven fast progressing myopic children between the ages of 4 to 12 years will be recruited. They will be stratified by 3 age groups: 4-6, 7-9 and 10-12, in a ratio of 1:2:1.

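### The protocol contradicts itself on allocation: age-stratified or simple randomisation, and whether the D1 group is randomised at all

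*Protocol*

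**What the plan says.** **Method.** The Section 1 synopsis, under Randomisation, says that "subjects will be Randomised to three groups at a ratio of 1:1 using a stratified randomisation based on age". Section 5.7, which describes how allocation is carried out, says: "Simple randomisation will be implemented by an unmasked Investigator by creating a column of random numbers for the group allocation using Microsoft Excel". It continues: "Eligible subjects will be assigned to one of the three groups in an equal ratio by following the random sequence generated from Excel". It then adds: "Age will be stratified by 3 groups: 4-6, 7-9 and 10-12, in a ratio of 1:2:1". The Study population paragraph of Section 1 uses nearly the same words about the children to be recruited: "They will be stratified by 3 age groups: 4-6, 7-9 and 10-12, in a ratio of 1:2:1".

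**Arms.** Section 1 (Randomisation) and Section 5.7 both refer to three randomised groups, and Section 5.17.2 has SV, D1 and D2 lenses ordered according to the randomisation. Section 5.6.1 is headed as a two-arm trial and says: "Eligible subjects will be randomly assigned to the control or the treatment group in an equal ratio". Section 5.6.2 makes D1 a Phase 2 auxiliary group, kept as an internal benchmark against D2: "an auxiliary group having the same number of subjects will be assigned to wear D1 lenses for 2 years". Sections 1 and 4 nevertheless list the efficacy of D1 against SV as a secondary objective.

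**Analysis.** Section 6.2 compares the primary and secondary outcomes by unpaired t-test, with no age term stated.

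**The concern.** Stratified and simple randomisation are different procedures. Stratifying by age serves to balance the arms within each age group, and this happens only if allocation inside the stratum is restricted, for example by blocks. A column of random numbers, with no list per stratum and no blocks described, does not ensure this, nor does it ensure the equal ratio that Section 5.7 also states. The 1:2:1 age ratio does not settle the matter, because Section 1 uses it to describe whom to recruit, so it may be only a quota. The planned t-test has no age term to offset chance imbalance on the one factor the trial chose to stratify by.

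The number of randomised arms matters more. If D1 is one of three arms allocated from the same sequence, D1 versus SV is a randomised comparison. If D1 is a separate group that is simply assigned, it is not, and neither is D1 versus D2. A reader of the protocol cannot tell which of these the trial will report.

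The protocol also describes no step that keeps the next allocation hidden until a child's eligibility has been recorded.

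**Working it through.** **1. The plan's own figures.** Section 6.1 uses a standardised difference of 0.658 and 90% power, two-sided. An exact two-sample t calculation (noncentral t) gives 50 per group at alpha 0.05 and 59 at alpha 0.025, as stated. Adding 10% gives 59 x 1.10 = 64.9, hence 65 (dividing by 0.9 gives 66). This point disputes none of these. They supply the totals used below: 3 x 59 = 177, the recruitment figure in Section 1, and 3 x 65 = 195.

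**2. Size of the 4-6 stratum.** At 1:2:1 it holds a quarter of the children: 195/4 is about 49 and 177/4 is about 44.

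**3. Imbalance under three readings of Section 5.7.** Let D be the D2 count minus the SV count in a stratum of n children, with three equal arms.

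- *Independent draws, 1/3 each.* The SD of D is sqrt(2n/3), which for n = 49 is 5.72. With a continuity correction, P(|D| >= 5) is about 2 x [1 - Phi(4.5/5.72)] = 0.43. Simulation agrees.
- *A fixed list of 65 per arm, shuffled without regard to age.* The variance is multiplied by (195 - 49)/(195 - 1), so the SD is 4.96 and P(|D| >= 5) is about 2 x [1 - Phi(4.5/4.96)] = 0.36. Simulation agrees.
- *A fixed equal list shuffled within each age stratum and used to its end.* |D| is at most about 1.

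| Reading | 4-6 stratum, differ by 5+ | by 8+ | Whole arms differ by 10+ |
|---|---|---|---|
| Independent draws, N = 195 (n = 49) | 43% | 19% | 41% |
| Independent draws, N = 177 (n = 44) | 41% | 17% | 38% |
| Equal list shuffled, age ignored, N = 195 | 36% | 13% | 0% |
| Equal list shuffled within stratum | 0% | 0% | 0% |

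Under independent draws, the share of children aged 4-6 differs between SV and D2 by at least 10 percentage points in about 19% of trials at N = 195 and 21% at N = 177.

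**4. Cost of unequal arms.** The noncentrality is d x sqrt(n1 n2/(n1 + n2)), with d = 0.315/0.475 = 0.663 and alpha 0.025. For 65/65 it is 0.663 x sqrt(32.5) = 3.78, power 93.3%. For 60/70 it is 0.663 x sqrt(4200/130) = 3.77, power 93.2%. At 59/59 and 54/64 the powers are 90.7% and 90.5%. Unequal sizes of this order cost almost nothing.

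**5. Status of D1.**

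| Points to three randomised arms | Points to two arms plus a separate group |
|---|---|
| Section 1, Randomisation: three groups | Section 5.6.1: two-arm heading, control or treatment |
| Section 5.7: one of three groups, from the random sequence | Section 5.6.2: Phase 2, auxiliary, assigned, internal benchmark |
| Section 5.17.2: SV, D1 and D2 ordered by randomisation | Section 5.6.2: recruitment criteria said to match those of Phase 1, as for a group recruited separately |
| Section 1: 177 = 3 x 59 | |

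The left-hand column has more entries, but Section 5.6 is where the design is set out. No text ranks one over the other, and no enrolment dates are given for D1.

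**The case against.** The best case for the protocol is that the fault is loose wording. Section 5.7 does mention age strata and an equal ratio. It speaks of a column of random numbers, not of one list for all ages, and sorting a fixed equal list on random numbers within each stratum would fit most of its words and leave almost no imbalance. That stands, and it is why the imbalance is given as a range. It does not remove the contradiction: Section 5.7 names the method as simple randomisation and describes no such restriction. It is also fair that chance imbalance in age under true randomisation is not bias, and that unequal arm sizes cost almost no power.

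Two stronger readings are tempting, and the protocol does not support them.

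- A reader might infer that D1 is recruited after the other groups, so that D1 versus SV is non-concurrent. The word Phase suggests it, but no text says so, and the study schematic, where timing might appear, is not reproduced in the copy reviewed.
- A reader might infer that allocation is foreseeable, because an unmasked investigator makes the list and it is followed in order. The protocol does not say who enrols children or who can see the list. It places randomisation after the baseline assessment, and it refers to a Manual of Procedures that is not at hand. Concealment is not described; that is all that can be said.

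**Conclusion.** The contradiction is real on both counts.

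On method, the protocol does not secure the age balance and equal ratio that it states. The probability of a difference of 5 or more between SV and D2 among children aged 4-6 runs from 43% (independent draws) through 36% (equal list shuffled without regard to age) to nil (equal list shuffled within stratum). These figures assume N = 195, a 1:2:1 age mix and three equal arms. D2 versus SV is randomised on every reading, so the primary comparison loses age balance and a little precision, but not validity. The method and the missing concealment step should be fixed.

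The status of D1 deserves more weight. Whether secondary objective i is a randomised comparison cannot be determined from the protocol, and that decides what may be concluded about D1 against SV. It does not follow that the comparison is non-randomised, only that the document leaves it open.

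**What to change.** Reconcile Section 1 (Study population and Randomisation) with Sections 5.6.1, 5.6.2, 5.7 and 5.17.2, so that they describe one scheme.

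- **Children not yet allocated:** 1:1:1 randomisation to SV, D2 and D1 by computer-generated permuted blocks within the three age strata, each allocation released only after eligibility is recorded. The REDCap system already in use is one way to do this. Say separately whether 1:2:1 is a recruitment quota.
- **Children already allocated:** state the method actually used, including how the next allocation was kept hidden, and adjust the primary and secondary comparisons for age group. New lists cannot change these allocations.
- **If D1 was not randomised alongside SV and D2:** label D1 versus SV and D1 versus D2 as non-randomised, adjust them for baseline age and spherical equivalent refraction, and draw no randomised efficacy conclusion from them.

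The cost is an amendment, the preparation of stratified lists if enrolment is still open, and one covariate in the analysis. No additional children are needed.
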